### Interim analyses {21b}

No formal interim efficacy analyses are planned. Recruitment and withdrawal rates will be reviewed during the trial on an ongoing basis. The independent DMC will review information on the progress and accruing data of the trial (e.g. recruitment rates, data quality, adherence to protocol treatment and follow-up, main study outcomes, and safety data) and provide advice on the conduct of the trial to the independent TSC. The TSC, on recommendation from the DMC, will have the ability to propose protocol changes, modify target recruitment, halt recruitment within a subgroup, and in exceptional circumstances prematurely terminate the trial. The Ministry of Defence will also have the ability to terminate the trial if, for example, it fails to deliver the required recruitment rate.

### Methods for additional analyses (e.g. subgroup analyses) {20b}

At present, no sub-group analyses are planned. Any that arise will be pre-specified in the SAP.

### Methods in analysis to handle protocol non-adherence and any statistical methods to handle missing data {20c}

The primary efficacy analysis will be based on the intention-to-treat principle in which all participants will be analysed according to the trial arm to which they were allocated, regardless of compliance. A secondary, sensitivity efficacy analysis will be carried out using imputation of missing data, if deemed appropriate based upon likely mechanism of ‘missingness’ and the degree of missing data. This will be specified in the SAP. The quantity of missing data will be reported, and a comparison made of those included in the primary analysis and those excluded due to missing data (either missing the primary outcome or baseline data for the analytical model).

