### Sample size {14}

A total sample size of 136 participants will be required (68 participants per trial arm, prior to accounting for drop-out), based on the primary outcome of an improvement in radiological healing by two Fredericson grades or more, or reduction to grade zero, 8 weeks after randomisation. The sample size was determined using data from Almirol and colleagues’ (2016) 8 week randomised controlled trial in adults aged 21–45 years with recent lower-extremity stress fractures (35). Almirol et al. (2016) reported 67% of participants who received teriparatide achieved a two grades or more improvement in healing or reduction to grade zero (i.e. ‘success’); compared with 43% of participants in the placebo group [35]. Assuming a 20% drop-out rate during the first 8 weeks of the present study, 108 participants (54 participants per trial arm) will complete an MRI scan at week 8; thereby providing 80% statistical power to detect a between group difference (two-sided test, significance level of 5%), if the ‘success’ rate is ≥ 71% in the intervention arm (chi-squared test with continuity adjustment). This equates to an odds ratio of 3.23 or a relative increase in healing of approximately 65%.

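### The primary analysis is described as intention-to-treat in all participants, but its own exclusion rule makes it complete-case, and the only imputation analysis is conditional

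*Protocol article*

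**What the plan says.** The section on non-adherence and missing data ({20c}) bases the primary efficacy analysis on the "intention-to-treat principle in which all participants will be analysed according to the trial arm to which they were allocated, regardless of compliance". Statistical methods {20a} repeats this, and Trial design {8} applies the intention-to-treat label without qualification.

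The last sentence of {20c} then promises a comparison between participants in the primary analysis and "those excluded due to missing data (either missing the primary outcome or baseline data for the analytical model". Exclusion for either reason is therefore part of the primary analysis as described. Imputation is a secondary sensitivity analysis, to be done "if deemed appropriate based upon likely mechanism of" the missingness and its extent, with the specification left to the SAP.

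Sample size {14} is built the same way. It starts from "A total sample size of 136 participants will be required (68 participants per trial arm, prior to accounting for drop-out"), takes a 20% loss by week 8, and rests power on the expectation that "108 participants (54 participants per trial arm) will complete an MRI scan at week 8".

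The model in {20a} contains the two stratification variables, fracture site, baseline MRI grade, trial arm, and any further baseline prognostic variables that the SAP names.

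**The concern.** The two statements in {20c} cannot both describe the same analysis. A reader of the trial report would take intention-to-treat in all participants to mean 136, while the rule delivers those with complete data.

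There are two consequences of different weight.

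- **Missing covariates.** A participant whose week 8 grade was observed is dropped if any baseline model variable is missing. This discards outcome data for no benefit.
- **Missing outcomes.** About a fifth of outcomes are expected to be missing in a trial where participants know their arm. Only the intervention arm has daily injections and the four-weekly checks tied to re-dispensing, so the reasons for leaving could differ by arm. If leaving also relates to healing, the complete-case estimate is biased. The one analysis that would fill in missing outcomes is not guaranteed to be run.

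**Working it through.** **Inputs from Sample size {14}:** 136 randomised (68 per arm), 20% drop-out to week 8, 54 per arm with an MRI, success 43% against 71%, two-sided 5%, continuity-adjusted chi-squared test, 80% power.

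**1. The plan's own figures.** 68 × 0.8 = 54.4, given as 54. Power with continuity correction is Φ{[|p₁−p₂| − 1/n − 1.96√(2p̄(1−p̄)/n)] / √[(p₁(1−p₁)+p₂(1−p₂))/n]}. With n = 54 and p̄ = 0.57 this is (0.280 − 0.0185 − 0.1867)/0.0914 = 0.82, so power is 79.3%. Exact enumeration gives 78.9%. The stated 80% reproduces within rounding, and the sample size already allows for the loss.

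**2. Expected exclusions.** 136 − 108 = 28, and 28/136 = 20.6% (14 per arm), before any loss through covariates.

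**3. Extra loss through covariates (assumed rates; the documents give none).** Losing a further 5% of completers leaves 51.3 per arm and 76.9% power. Losing 10% leaves 48.6 per arm and 74.2% power.

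**4. Illustration of outcome-dependent loss (assumed rates).** The observed success rate is p(1−mₛ)/[p(1−mₛ)+(1−p)(1−m_f)], where mₛ and m_f are the proportions missing among successes and failures. Controls are set at 20% for both, so 43% stays 43%.

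- Intervention arm, p = 0.71, mₛ = 0.10, m_f = 0.45: 0.639/(0.639 + 0.1595) = 80.0%. The observed difference is 37 points against a true 28. Missingness in that arm is 1 − 0.7985 = 20%, the same as in controls, so equal drop-out by arm would not reveal the bias.
- No true effect, p = 0.43, same rates: 0.387/(0.387 + 0.3135) = 55.2%. The spurious difference is 12 points, with 30% missing in the intervention arm.

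**5. Would ordinary imputation repair this?** In the first scenario the missing intervention participants comprise 0.071 successes and 0.1305 failures, so 0.071/0.2015 = 35% succeeded. Imputation from the observed participants in the same arm, without informative auxiliary variables, would fill them in at about 80% and so largely return the 37 points. A departure set separately by arm is needed to examine this case.

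**6. How far 14 missing per arm could move a result (assumed counts near the planned rates; unadjusted continuity-corrected tests, not the planned model).**

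| Handling of the missing | Intervention | Control | Difference | p |
|---|---|---|---|---|
| Complete case | 38/54 | 23/54 | 27.8 points | 0.007 |
| All missing counted as not improved | 38/68 | 23/68 | 22.1 points | 0.016 |
| Only missing controls improved | 38/68 | 37/68 | 1.5 points | 1.0 |
| Only missing intervention participants improved | 52/68 | 23/68 | 42.6 points | <0.001 |

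If 6 of the 14 missing controls improved (the 43% rate), significance is lost when 3 or fewer of the 14 missing intervention participants improved (3: p = 0.059; 4: p = 0.039). The last two table rows are limits, not forecasts.

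**The case against.** **Intention-to-treat is tied here to allocation and compliance, and the exclusion is disclosed in the same section.** This is fair. Everyone with data is analysed in the allocated arm, and participants who stop treatment are followed if willing. A reader might infer that the plan departs to an analysis by treatment received; it does not. The fault lies in the claim to include all participants and in the exclusion rule.

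**Imputation is deferred to the SAP.** Its method and trigger are, and the SAP goes to the DMC and TSC for approval before the final data lock. A reader might infer that the decision to impute will be taken after seeing missingness by arm. The text does not establish that, since the SAP could fix a threshold in advance. The complete-case rule and the conditional status of imputation, however, stand in the article itself.

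**Covariate loss is speculative.** Largely so. The strata are needed to randomise, and site and grade should come from the diagnostic MRI. Loss would arise mainly from further prognostic variables, none of which is named yet. The rule is still inferior to its replacement, which costs almost nothing.

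**Later scans are already used.** The generalised estimating equation analysis in {20a} does use MRI grading at every time point, without condition. It would be wrong to say that the week 10 to 16 scans are ignored, or that they nearly settle week 8 status: a fracture at grade zero at week 10 may not have met the criterion at week 8, and someone who has left the trial has no later scans. That analysis does not by itself deal with outcome-dependent drop-out.

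**Complete-case logistic regression can be valid.** It is, if only outcomes are missing and missingness depends only on arm and model covariates. Some of the loss also looks administrative. According to Trial status, participants recruited before the March 2020 pause were to be withdrawn by calendar date without an in-person week 8 assessment; their number is not given. So bias is possible but not shown, and the 45%/10% rates have no source in the documents.

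**Conclusion.** The point holds in a limited form. The article promises an analysis of all participants and describes a complete-case one, expected to omit about 28 of 136 (20.6%). That share is the plan's own drop-out assumption, not an observed rate. The only analysis that would impute missing outcomes is conditional.

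The covariate exclusion probably costs little: about 2 to 5 points of power at assumed further losses of 5% to 10%. The direction and size of any bias from missing outcomes are unknown. The rise from 28 to 37 points rests wholly on assumed, outcome-dependent missingness and shows what could happen, not what will. A reader might go further and conclude that the primary estimate is biased or the sample size wrong. The documents support neither.

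**What to change.** 1. In {20a} and {20c}, define the primary analysis set as all randomised participants with a week 8 grade, analysed in the allocated arm. Replace the exclusion for missing baseline data with a simple fill of baseline covariates (mean or mode, or a missing indicator), made without regard to arm, so that nobody with an observed outcome is dropped.
2. Remove the condition on the sensitivity analysis and always report it beside the primary result. It should impute the week 8 outcome in all randomised participants by multiple imputation, using arm, the model covariates, and whatever pain scores and later MRI grades are available. Add an arm-specific delta or tipping-point analysis, because imputation under missing-at-random would not address outcome-dependent drop-out. The imputation model and the range of deltas can be set in the SAP.

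The cost is a wording change and a little extra analysis work. No new data are needed and the sample size is unchanged.

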### Plans to give access to the full protocol, participant level-data and statistical code {31c}

Requests for access to the full protocol, data, and statistical code will be considered, and approved in writing where appropriate, after formal application to the TMG or TSC. After completion of the trial, applications can be made to NCTU.

## Oversight and monitoring

### Composition of the coordinating centre and trial steering committee {5d}

#### Trial Team

The Chief Investigator, Trial Manager and the NCTU will be responsible for the day-to-day running of the trial and implementing trial-specific processes. They will work together with representatives from the Ministry of Defence as the Trial Team.

#### Trial Management Group

The TMG (Sponsor Representative, Chief Investigator, and Ministry of Defence, NCTU and University of East Anglia co-investigators) will assist with developing the design, coordination and strategic management of the trial.

#### Trial Steering Committee

The TSC will be the independent group responsible for oversight of the trial and ensuring it is performed according to Good Clinical Practice in order to safeguard participants. The TSC will provide advice to the Chief Investigator, NCTU, the funder (Ministry of Defence) and Sponsor (NNUH) on all aspects of the trial through its independent chair.

### Composition of the data monitoring committee, its role and reporting structure {21a}

#### Data Monitoring Committee

The DMC will be independent from the Sponsor and competing interests and will be the only oversight body that has access to accumulating comparative data. The DMC will be responsible for safeguarding the interests of participants, monitoring the accumulating data, and making recommendations to the TSC on whether the trial should continue as planned. The DMC will consider data in accordance with the SAP and will advise the TSC through its chair.

### Adverse event reporting and harms {22}

The definitions of harm according to the European Union directive 2001/20/EC Article 2 and detailed guidance laid out in 2011/C172/01, based on the principles of the International Council for Harmonisation for Good Clinical Practice, will be applied in the RETURN trial. All adverse events and reactions will be assessed for seriousness, causality, severity and expectedness and will be reported to the relevant regulatory bodies. Any unfavourable and unintended sign, symptom or illness that develops or worsens during the study (and for 4 weeks after a participant’s final visit) will be classified as an adverse event, whether or not it was considered to be related to the study intervention. Adverse events will include unwanted side effects, sensitivity reactions, abnormal laboratory results, injuries and inter-current illnesses, and may be expected or unexpected. All events will be followed until resolution. There will be no exempted adverse events in this trial. A notifiable event will be grade 3 (or higher) haematological toxicity (according to Common Terminology Criteria for Adverse Events v5.0), identified in blood tests whilst a participant is taking trial medication. The TMG will review line listings of cumulative serious adverse events. Any concerns about potential emerging toxicity will be escalated to the independent DMC. The DMC will review safety data including reported frequencies of non-serious adverse events, serious adverse reactions and suspected unexpected serious adverse reactions.

### Frequency and plans for auditing trial conduct {23}

The frequency, type and intensity of routine and triggered on-site monitoring will be detailed in the quality management and monitoring plan. On-site visits will be arranged every 6 months, or more frequently if concerns are raised by the Trial Team, Sponsor or TMG. Site monitoring will be performed by a member of NCTU delegated to perform monitoring tasks. The quality management and monitoring plan will also detail the procedures for review and sign-off of monitoring reports.

### Plans for communicating important protocol amendments to relevant parties (e.g. trial participants, ethical committees) {25}

Amendments to the protocol will be agreed by the TMG and submitted to MODREC for approval. Amendments will not be implemented until approvals from the Medicines and Healthcare products Regulatory Agency (MHRA) and Health Research Authority have also been received, and research sites have confirmed their acceptance with NCTU. The public study record on ClinicalTrials.gov will be updated with protocol amendments.

### Dissemination plans {31a}

The results of the trial will be disseminated regardless of the direction of effect and will be reported according to the Consolidated Standards of Reporting Trials statement [49]. Results of the trial will be disseminated by publication in appropriate journals and conference presentations. Permission to publish from the Ministry of Defence will be required prior to publication. A lay summary of the trial results will be given to all participants at the end of the study.

## Discussion

The RETURN trial will be the first study to investigate the effect of teriparatide on lower body stress fracture healing in young, otherwise healthy men and women. The use of MRI and blinded review using the validated Fredericson stress fracture classification system will enable radiological healing to be examined as the primary and as a secondary study outcome [39, 40]. As the gold standard for assessment of bone stress injury, MRI has been shown to be the most sensitive and specific imaging test for diagnosing lower body stress fractures [50] and will, therefore, allow injury severity and recovery progress to be closely monitored. In addition, MRI is non-invasive and will not expose participants to ionising radiation, in contrast to conventional radiology, nuclear scintigraphy and computed tomography [50]. The protocol of two-weekly MRI scans from weeks 8–16, and four-weekly from weeks 16–24, until fracture healing, will enable the time to radiological healing to be captured with greater accuracy than in previously published literature [27–30, 32, 33, 35]. By using MRI to assess healing, the efficacy of teriparatide will be examined using an outcome that participants and reviewers are unable to manipulate.

The recovery of participants’ physical function and health will be assessed using a variety of methods. Using a clinical severity score to assess clinical healing once a fracture is radiologically healed will enable a standardised assessment of physical function to be made [41]. In addition, the time to discharge from physical rehabilitation will provide a measure of physical function and readiness to return to training. The time to discharge from physical rehabilitation will be affected by confounding variables e.g. (i) the physical demands of the training course the participant is re-joining, determined by the week of training at the time of injury, and the physical intensity of their regiment’s training programme; and (ii) the participant’s compliance to, and engagement with, their rehabilitation programme. Although reliant on self-report, the pain visual analogue scale and SF-36 are relatively easy to complete and will add minimal additional burden to participants. The visual analogue scale has been shown to be a valid and reliable tool to assess pain [42, 43] and will be interpreted alongside the participant’s record of analgesic use. The widely used SF-36 will provide a valid and reliable measure of health-related quality of life, functional health and wellbeing [44, 45]. The inclusion of assessments of blood and urine biochemistry; bone density and morphology; and physical activity levels will provide an insight into the mechanisms underlying the hypothesised beneficial effect of teriparatide on stress fracture healing. Participants’ alcohol consumption, smoking habits and physical fitness (confounding factors for skeletal health [46]) will be recorded so the possible effect of these variables on study outcomes can be analysed.

One of the challenges associated with the collection of the outcome measures is the burden placed on participants. To mitigate trial burden, study visits will be scheduled to avoid disruption to participants’ Army training and physical rehabilitation programme, and with transport provided as required. In addition, the week 4 study visit, when many participants are expected to be on sick leave, will be completed at the participant’s home if required. The requirement for participants to be undergoing Phase One or Two Army training, and focus on Infantry training in particular, means a standardised rehabilitation programme will be followed by all participants. This will enable the efficacy of teriparatide to be examined with greater control over confounding variables, such as variation in rehabilitation programmes and access to facilities, than would likely be possible among athletic or civilian cohorts.

### Safety

One safety concern associated with teriparatide during its development was the possible association with osteosarcoma, due to a preclinical animal study reporting a dose-dependent increase in the incidence of osteosarcoma and some other rare bone tumours in one breed of rat, treated with near life time, high doses of teriparatide [25]. This finding was not observed in subsequent animal studies with other animal models or breeds of rat, and treatment with teriparatide in humans has been demonstrated to be safe, with no association between teriparatide and osteosarcoma observed since surveillance studies commenced in 2003 and 2009 [24–26]. The maximum total duration of treatment with teriparatide was increased from 18 to 24 months by the European Medicines Agency and US Food and Drug Administration based on safety data and post-marketing experience [51, 52].

For safety, participants’ blood and urine samples, collected at baseline and every 4 weeks throughout the study, will be analysed to ensure they are within adult reference ranges (analytes listed in Table 1). Hypercalcaemia and hypercholesterolaemia have been reported in individuals treated with teriparatide [24]; hence, serum calcium and total cholesterol will be monitored throughout the study. Teriparatide may cause small increases in urinary calcium excretion [24]; thus, participants’ urine calcium will be monitored. Participants will be expected to be otherwise healthy because in order to be undergoing Army training, they will have recently passed a physician screened medical assessment.

Teriparatide should not be given to individuals with open epiphyses [24]; thus, potential participants who present with open epiphyses in their diagnostic MRI scan will be excluded from participating. Signs of depression will be monitored using the C-SSRS because depression is a possible side effect of treatment with teriparatide [24]. Women will require a negative serum pregnancy test result to be eligible to participate and must agree to use of a highly effective form of contraception (failure rate < 1% per year, e.g. combined oestrogen and progestogen, or progestogen-only hormonal contraception, or intrauterine device) because teriparatide is contraindicated for use during pregnancy [24]. Treatment with teriparatide will be discontinued for participants who become depressed or pregnant. A negative urine pregnancy test result will be required prior to teriparatide re-dispensing. Dual-energy X-ray absorptiometry, pQCT, and HR-pQCT scans will expose participants to ionising radiation, however, the total radiation exposure for each participant will be relatively low, categorised as minor risk (0.1–1 mSv; Category IIa) [53]. A negative pregnancy test result will be required before DXA, pQCT, and HR-pQCT scans to avoid exposing pregnant women to ionising radiation.

